### 1.1. Assessment

In Denmark, the assessment and treatment program at the National Gender Identity Service, including semen cryopreservation, is part of the National Health Service [7]. Individuals under the age of 18 years with gender identity concerns can be directly referred by general practitioners or other health care professionals without prior evaluation.

Before the age of 10 years, parents or guardians are offered reflective consultations to help them support their child. After the age of 10 years, the youngster is offered either a full assessment program or psychosocial support following an initial screening visit, during which the gender incongruence and its duration are assessed. The full assessment program is then initiated if indicated.

The psychosocial support program consists of two or three in-person sessions with the youngster that include reflections on gender, body image, and sexuality. After these sessions, the youngster is concluded from the service.

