The full assessment program comprises a minimum of five in-person consultations at the Sexological Clinic, aimed at exploring the youngster’s history of gender identity concerns, body image, wishes for treatment, development of sexuality, and overall well-being. The youngster’s parental support and peer network are also assessed. At the Child and Adolescent Mental Health Centre, a psychiatric screening for any psychopathology, an evaluation of cognitive function, and an assessment of the global level of functioning are conducted simultaneously. Based on the results of the psychiatric screening, additional psychological testing is then performed using well-validated tests, with supporting psychometric studies published between 1938 and 2023. The family is also seen at the pediatric endocrinologic department for information on hormone therapy possibilities, their effects, and potential risks. When the full assessment is completed, an MDT conference is held to discuss a treatment plan, including a decision on whether puberty blockers or GAHT can be offered. If no consensus is achieved, further counseling sessions may be necessary. Additional MDT conferences are held each time the treatment plan needs to be revised, such as for the initiation of GAHT after puberty suppression with GnRHa monotherapy or deciding on referral to mastectomy at the age of 18 years. Consultations addressing gender identity, well-being, and psychosocial effects of treatment continue after the initiation of hormone therapy [57].

See Figure A1 for assessment and treatment pathways.

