## 2. Materials and Methods

### 2.1. Experimental Design

This protocol describes a retrospective observational study conducted in a national cohort from a single tertiary medical center. The study population includes all individuals under 18 years of age who were referred to and attended at least one appointment at the Gender Identity Service in Copenhagen from 1 January 2016 to 1 January 2023. There are no exclusion criteria.

The study collects longitudinal data from medical records on the experiences with and development of gender identity, gender incongruence, and sexuality for all individuals in the study population. Furthermore, the study gathers information on the social context of the youngsters, such as demographics, socioeconomic status, family circumstances, school attendance, and social networks. Mental health data collection encompasses psychiatric symptoms and diagnoses, results of psychological tests, suicidal thoughts, substance abuse, and global level of functioning. Physical health data collection includes hormone therapy type, its effects and side effects, anthropometry, DXA scans, blood samples, and semen cryopreservation. Data on discontinuation of hormone therapy and treatment trajectories are also collected. See Appendix A Table A1 and Table A2 for details on data collection.

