### 2.4. Analysis Plan

Data will be extracted from the REDCap database and analyzed in pseudo-anonymized datasets. Descriptive statistics will be used for sociodemographic characteristics, physical and mental health profiles, and treatment trajectories, i.e., mean (SD), median (IQ range), and frequencies (proportion). The data will be divided into subgroups according to whether hormone therapy is offered before the age of 18 years and whether they are referred to the Gender Identity Service before or after the onset of puberty. The subgroups will be compared according to sex assigned at birth, age of onset of gender incongruence, social transition, as well as sociodemographic background, mental health profiles, and global level of functioning. Physical health profiles of the youngsters in the hormone therapy subgroup will be compared to normative age- and relevant gender-matched reference populations. Group comparisons will be made using the Student’s *t*-test and Mann–Whitney/Wilcoxon tests as appropriate. Changes over time will be analyzed using time trend analysis for related data and paired *t*-tests or mixed model analysis. Regression models will investigate confounding factors related to treatment/no treatment outcomes and basic characteristics. If appropriate, analyses will be reported by year, i.e., trends in referral patterns and decision algorithms.

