Suicide attempts	Yes, current/yes, prior/no
Self-reported psychiatric symptoms	
Traits of psychiatric disease	Yes, current/yes, prior/no
Psychiatric morbidity	
Prior registered diagnoses	Yes/no
Consultation at a child and adolescent psychiatric emergency room	Yes/no
Admitted to a child and adolescent psychiatric hospital	Yes/no
Pharmacological psychiatric treatment	Yes/no
Substance abuse	
Alcohol abuse	Yes, current/yes, prior/no
Smoking	Yes, current/yes, prior/no
Drug abuse	Yes, current/yes, prior/no
Self-medication	
Testosterone/estrogen/other	Yes/no
**Psychiatric Evaluation Variables**	**Value**
Psychiatric morbidity	
Registered diagnoses	Yes/no Diagnosis codes
Pregnancy and birth	Normal/abnormal
Early psychomotor development	Normal/abnormal
Psychological tests and evaluations (on indication)	K-SADS (Kiddie Schedule for Affective Disorders and Schizophrenia) [63] PSE (Present State Examination) [64] SRS-2 (Social Responsiveness Scale) [65] BRIEF (Behavior Rating Inventory of Executive Function) [66] ADHD-RS (ADHD-Rating Scale) [67] WISC 4/5 (Wechsler Intelligence Scale for Children) [68] WAIS 4 (Wechsler Adult Intelligence Scale) [69] ADOS (Autism Diagnostic Observation Schedule) [70] ADI-R (Autism Diagnostic Interview-Revised) [71] ABAS (Adaptive Behavior Assessment System) [72] SCID (Structured Clinical Interview for DSM-5 Personality Disorder) [73] Roberts [74] Rorschach [75] C-GAS (Children’s Global Assessment Scale) [76] GAPD (Global Assessment of Psychosocial Disability) [77]
**Treatment Trajectory Variables**	**Value**
Healthcare use	
Total number of visits	Number
Date of first visit	Date (DD-MM-YYYY)
Date of last visit	Date (DD-MM-YYYY)
Outcome of assessment (multidisciplinary conference decision on GAHT)	Yes/no/other
Date of discharge from Gender Identity Service	Date (DD-MM-YYYY)
**Visits Variables**	**Value**
Repeated measures	
Changes in any listed variable	

**Table A2 jcm-13-06658-t0A2:** List of treatment variables to be extracted for analysis for youngsters who attended at least one appointment at the Danish Gender Identity Service from 2016 through 2022.

Treatment Variables	Value
Basis, Department of Growth and Reproduction	
Date/age at referral for information only	Date (DD-MM-YYYY)/age in years (number)
Date/age at visit for information only	Date (DD-MM-YYYY)/age in years (number)
Date/age at referral for hormone therapy	Date (DD-MM-YYYY)/age in years (number)

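### Psychiatric diagnoses and functioning are compared by hormone offer across the whole cohort, but screening for them is described only in the full-assessment pathway

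*Protocol article*

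**What the plan says.** The population in section 2.1 is "all individuals under 18 years of age who were referred to and attended at least one appointment", with no exclusions. Section 2.4 then states: "The data will be divided into subgroups according to whether hormone therapy is offered before the age of 18 years". A second split is by referral before or after puberty onset. The subgroups are compared on birth-assigned sex, onset of incongruence and social transition, "as well as sociodemographic background, mental health profiles, and global level of functioning".

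Section 1.1 describes three routes through the service:

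- **Under 10:** "Before the age of 10 years, parents or guardians are offered reflective consultations to help them support their child".
- **Psychosocial support (from age 10):** an initial visit looks at the incongruence and how long it has lasted. After that, "The psychosocial support program consists of two or three in-person sessions with the youngster that include reflections on gender, body image, and sexuality". Contact with the service then ends.
- **Full assessment (from age 10):** at least five consultations at the sexological clinic. The psychiatric part of the programme is worded as follows: "a psychiatric screening for any psychopathology, an evaluation of cognitive function, and an assessment of the global level of functioning are conducted simultaneously". Further psychological testing depends on that screening. The multidisciplinary (MDT) conference that decides on hormones follows completion.

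Appendix A, Table A1, puts C-GAS and GAPD in a list whose label begins "Psychological tests and evaluations (on indication". It also records "Changes in any listed variable" at repeated visits.

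**The concern.** Whether a new psychiatric diagnosis, a test score or a functioning score exists depends on the route a youngster took. The route in turn largely determines the comparison group: on the described pathway everyone offered hormones has been screened, while part of the not-offered group has not. Group and ascertainment are therefore confounded by construction.

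The contrast between youngsters who do and do not receive hormone therapy is one the introduction calls for, and section 3 says the findings are meant to shape assessment and treatment protocols. A morbidity difference produced by looking harder in one group could be read as a clinical difference. The planned regression addresses confounding factors and cannot recover outcomes that were never ascertained.

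**Working it through.** The article states no sample size, power or prevalence for this comparison, so there is no figure to reproduce. The check has three steps.

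**1. Who is measured for what**

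| Route (section 1.1) | Screening and functioning described? | Group in section 2.4 |
|---|---|---|
| Full assessment, hormones offered | Yes | Offered |
| Full assessment, hormones not offered | Yes | Not offered |
| Psychosocial support only | No | Not offered |
| Under 10, parental consultations only | No | Not offered |

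The share of the not-offered group in the last two rows is not given.

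**2. New diagnoses: possible size**

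All inputs here are assumptions. Let π be the true prevalence, equal in both groups; s1 the chance that a condition is recorded if screened; s0 the chance if not screened; and f the unscreened share of the not-offered group.

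- Recorded in offered group = π × s1
- Recorded in not-offered group = π × [f × s0 + (1 − f) × s1]
- Spurious gap = π × f × (s1 − s0)

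With s1 = 90% throughout:

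| π | s0 | f | Offered | Not offered | Gap | Odds ratio |
|---|---|---|---|---|---|---|
| 20% | 70% | 25% | 18% | 17% | 0.20 × 0.25 × 0.20 = 1 point | 1.07 |
| 40% | 50% | 50% | 36% | 28% | 0.40 × 0.50 × 0.40 = 8 points | 1.45 |
| 40% | 50% | 75% | 36% | 24% | 0.40 × 0.75 × 0.40 = 12 points | 1.78 |

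To see how often such a gap would reach two-sided p < 0.05, take N = 1300 with 30% to 50% offered hormones. The introduction reports more than 1300 referred; the number who attended is not given, and the offered share is assumed. The chance is 7% in the first row, 81% to 87% in the second and 99% or more in the third. If only fully assessed youngsters are compared, f = 0, the gap is 0 and the rejection rate returns to 5%. This assumes equal detection in both groups once screened.

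**3. Items listed for all attendees**

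Table A1 lists self-harm, suicidal thoughts, substance use, prior registered diagnoses, psychiatric admission and emergency contact outside the psychiatric evaluation block. Here only unequal contact matters. Assume 40% true prevalence, a chance p that any one visit documents the item, independent visits, four visits in psychosocial support (the initial visit plus three sessions) and ten in the offered group:

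- p = 30%: 0.40 × (1 − 0.7⁴) = 30.4% against 0.40 × (1 − 0.7¹⁰) = 38.9%, a gap of 8.5 points
- p = 50%: 37.5% against 40.0%, a gap of 2.5 points

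If half the not-offered group also had ten visits, the 8.5 points fall to about 4. Ten visits and the values of p are assumed.

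**The case against.** The strongest reply is that the not-offered group is mixed. It includes youngsters who completed the full assessment without an offer, which dilutes any bias by an unknown amount. The two relevant aims in section 1.3 are to describe prevalence, and section 4 presents the study as hypothesis-generating. This stands as a limit on size and urgency. It does not remove the problem, because section 2.4 and the abstract commit to a between-group comparison and state no restriction to those assessed.

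A reader might go further and infer any of the following. The documents do not support them:

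- **That differences are certain, or that most of the comparison group was unscreened.** Neither the share nor the detection rates are stated.
- **That every mental health item is equally affected.** The screening argument covers only new diagnoses, tests and functioning scores.
- **That functioning is biased in a known direction.** Selective missingness has none that can be fixed in advance.
- **That undocumented items are entered as no.** Table A1 prints substantive values in a condensed article, and section 4 expects missing data. How blanks are coded belongs in a codebook that is not shown.

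Listing C-GAS and GAPD among tests done when indicated may be only loose labelling in a long table cell. It still conflicts with section 1.1, where functioning is part of every full assessment.

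Section 4's statement that the single-centre design limits bias from assessment practices is reasonable for differences between centres. It does not hold for differences between routes within the service, and the general caveat about missing records does not mention them.

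**Conclusion.** The concern holds and should be fixed. As written, the offered versus not-offered comparison of new psychiatric diagnoses mixes true differences with differences in who was screened, most likely making diagnoses look more frequent in the offered group. With equal true prevalence, the spurious gap is roughly 1 to 12 percentage points over the assumed range (prevalence 20% to 40%, unscreened detection 50% to 70% against 90% if screened, unscreened share 25% to 75%). Test and functioning scores will be selectively missing, with no predictable direction. Items recorded for all attendees are affected less, through unequal contact alone. The structural point rests on the care pathways as section 1.1 describes them; the sizes are illustrations and not estimates for this cohort.

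**What to change.** 1. Compare newly registered diagnoses, test results and C-GAS/GAPD only among youngsters who completed the full assessment, offered versus not offered, using values recorded up to the first MDT conference.
2. For whole-cohort comparisons, use items that exist whatever the route, such as prior registered diagnoses and prior psychiatric admission or emergency contact, taken from the initial contacts. Describe the psychosocial-support and under-10 routes separately, with the number assessed. An MDT-based cut-off should not be applied to them, since no conference is described for those routes.
3. Do not present results of tests done only when indicated as cohort prevalence. Reconcile section 1.1 with Table A1 on whether functioning is assessed in every full assessment.
4. In section 4, replace the claim that the design limits bias from assessment practices with a statement that ascertainment depends on pathway.

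The main cost is a smaller comparison group for diagnoses and functioning, and a narrower question: those results would apply to fully assessed youngsters, not to all attendees. Otherwise the change is mostly analysis-plan and limitations wording. Table A1 already lists the MDT outcome, the number of visits, and prior diagnoses separately from registered ones. As printed it shows no date for the MDT conference, so that date may need to be extracted if the database does not hold it.

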### 1.3. Aims

This study aims to:describe the sociodemographic background of TGD individuals under 18 years of age referred for evaluation of gender incongruencedescribe the development of gender identity and incongruenceinvestigate the impact of social transitioning on gender identity (social transition is defined in this protocol as living in accordance with one’s experienced gender identity)describe the development of sexualitydescribe the physical health characteristics, including short-term and long-term clinical effects, safety, and efficacy of hormone therapydescribe the mental health characteristics, such as the prevalence of psychiatric disorders and the global level of functioningdescribe the prevalence of substance abuse, self-harm, and suicidal ideationexplore the well-being of youngsters offered hormone therapy until their discharge from the team at the age of 18 yearsdescribe the number, characteristics, and reasons for youngsters who detransitioned, discontinued and/or regretted hormone therapy before being discharged from the team at the age of 18 yearsdescribe trends and changes in the diagnostic process and treatment trajectories in the study period.

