**Semen cryopreservation—repeated measures**	
Date/age of semen collection	Date (DD-MM-YYYY)/age in years (number)
Azoospermia	Yes/no
Volume	Number (mL)
Concentration	Number (mill/mL)
Progressive motility spermatozoa	Percentage (%)
Non-progressive motility spermatozoa	Percentage (%)
Immotile spermatozoa	Percentage (%)
Did not complete semen collection	True/false
**Visits—repeated measures variables**	**Value**
Date of visit	Date (DD-MM-YYYY)
Blood pressure	Systolic blood pressure (number) Diastolic blood pressure (number)
**Other clinical data variables**	**Value**
Dual-energy X-ray absorptiometry (DXA) scan	Bone mineral density (BMD) (g/cm^2^) + Z-scores Total body fat percentage (%) Regional body fat percentage (%) Lean body mass (LBM) (g)
Growth chart	Height (cm) + standard deviation score (SDS) Weight (kg) + SDS Growth velocity (cm/year) + SDS Predicted adult height (cm) + SDS Target height (cm) + SDS
Bone age (a.m. Greulich-Pyle, BoneXpert)	Age in years (number)
Routine blood samples	Reproductive hormones Growth factors Thyroid hormones Vitamin D Lipids Liver-kidney function tests Hematocrit Hemoglobin
Biobank	Serum, plasma, DNA

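### The efficacy wording of the fifth aim goes beyond a within-person change analysis that is not tied to age norms; for lean mass, body fat and blood pressure, normal maturation could be read as a treatment effect

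*Protocol article*

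**What the plan says.** The fifth aim in section 1.3 is to describe physical health characteristics, including "short-term and long-term clinical effects, safety, and efficacy of hormone" therapy. Section 2.1 sets the design: "This protocol describes a retrospective observational study conducted in a national cohort from a single tertiary medical center".

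Section 2.4 gives three analysis elements that bear on this aim:

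- Change: "Changes over time will be analyzed using time trend analysis for related data and paired" t-tests or mixed model analysis. The sentence names no comparator and no term for age or puberty.
- Norms: "Physical health profiles of the youngsters in the hormone therapy subgroup will be compared to normative age- and relevant gender-matched reference populations".
- Treated versus untreated: "Regression models will investigate confounding factors related to treatment/no treatment outcomes and basic characteristics".

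Appendix A, Table A2, lists Z-scores for bone mineral density and SDS for height, weight, growth velocity, predicted adult height and target height. Body composition appears as fat percentages and as "Lean body mass (LBM) (g", and blood pressure as "Systolic blood pressure (number) Diastolic blood pressure (number"; none of these has a standardised score. Section 1.2 allows puberty suppression from Tanner stage 2 and puts DXA scans two years apart. On the psychosocial support route, section 1.1 says: "After these sessions, the youngster is concluded from the service".

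**The concern.** Efficacy is a causal word: it means that the outcome differs from what would have happened without treatment. In adolescents who may still be growing, lean mass, fat distribution and blood pressure can change with age whether or not a drug is given. A paired t-test asks only whether the mean change is zero, so it rejects when maturation alone moves the mean.

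An internal untreated series of physical measurements would help, but the article describes none. The somatic work-up in section 1.2 is done before hormone therapy and its elements are repeated at treatment visits, and the subgroup comparisons in section 2.4 do not list physical outcomes. The age-matched norms could supply the expected course, but the plan applies them to profiles and does not carry them into the change analysis.

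This matters because the authors want the results to inform treatment guidelines (section 1). The introduction also names body composition and cardiovascular risk as open questions, and these are the outcomes that Table A2 lists in raw units only.

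**Working it through.** The plan states no sample size, SD, alpha or expected change, so there is no figure of its own to reproduce. The check has two parts.

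**1. Which outcomes are exposed**

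| Outcome (Table A2) | Standardised score listed? | Exposed to maturation in a paired test? |
|---|---|---|
| Bone mineral density | Z-score | Only if g/cm² is the value tested |
| Height, weight, growth velocity | SDS | Only if the raw value is tested |
| Lean body mass (g) | No | Yes |
| Total and regional body fat (%) | No | Yes |
| Blood pressure | No | Yes |

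**2. How large the effect could be (illustration; two-sided 5%, zero drug effect)**

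Let d be the mean change due to maturation divided by the SD of the change. The paired t statistic is then noncentral t with n − 1 degrees of freedom and noncentrality d√n. The rejection rates are:

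| n | d = 0 | d = 0.1 | d = 0.2 | d = 0.3 |
|---|---|---|---|---|
| 50 | 5% | 11% | 28% | 55% |
| 100 | 5% | 17% | 51% | 84% |
| 200 | 5% | 29% | 80% | 99% |
| 400 | 5% | 51% | 98% | about 100% |

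The column d = 0 is the case of a standardised score that tracks its reference.

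For lean mass, assume a natural gain of g kg per year over the two-year DXA interval. Then t = 2g / (SD/√n).

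| g (kg/year) | SD of change (kg) | n | t |
|---|---|---|---|
| 0.5 | 4 | 100 | 1.0/0.40 = 2.50 |
| 0.5 | 4 | 50 | 1.0/0.566 = 1.77 |
| 0.5 | 6 | 100 | 1.0/0.60 = 1.67 |
| 3 | 4 | 100 | 6.0/0.40 = 15.0 |

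These are expected t values, against a critical value of about 2. In the first row d = 1/4 = 0.25, so rejection is likely (roughly 70%) but not certain. The second and third rows fall short of significance on average. Only the two-year interval comes from the article; g, SD, n and alpha are assumptions.

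**The case against.** A reader might infer that the study is uncontrolled and that normal growth will be counted as a treatment effect. The article does not support that reading. No sentence says that efficacy will be concluded from paired tests alone, and the word sits inside an aim to describe. The study calls itself observational and hypothesis-generating (sections 2.1 and 4). Section 2.4 plans a comparison with age- and gender-matched norms, and nothing confines it to baseline. It also offers mixed models, which can carry age. Bone mineral density, where slow raw accrual could be mistaken for a gain, already has a Z-score.

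Further points stand. Table A2 lists variables for extraction, not analysis scales, and covariates may be set in a fuller analysis plan that is not shown; their absence here is not an error in itself. Some listed effects, such as voice deepening in transmasculine and breast development in transfeminine youngsters, are not plausibly explained by natural maturation. The psychosocial support route is not the only untreated group: a full assessment may also end without an offer of gender-affirming hormone therapy. So the lack of an untreated series can be claimed only for serial physical measurements. Nor would a false finding be significant under every assumption, as the lean-mass table shows.

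These points narrow the concern but do not remove it. The article offers a plain paired t-test on an equal footing with the mixed model, leaves the norms unconnected to change, and uses a word that neither analysis can support. Agreement with or departure from norms accounts for expected maturation, but it does not control for who was selected for treatment.

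**Conclusion.** The point holds in a limited form. For physical outcomes, the article describes within-person change in treated adolescents, some still growing, plus a normative comparison of profiles that is not tied to that change. For lean mass, body fat and blood pressure, following section 2.4 as written could mix normal maturation with treatment change. For bone mineral density, height, weight and growth velocity the risk arises only if raw values are tested.

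The size cannot be taken from the article. Under the assumptions above, false rejection ranges from 11% (n = 50, drift 0.1 SD) to nearly 100% (n = 400, drift 0.3 SD), against a nominal 5%. Drift would be smaller in participants late in puberty. Efficacy overstates what this design can show whatever the drift.

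**What to change.** 1. In the fifth aim, replace efficacy with changes observed during hormone therapy.
2. In section 2.4, make change in the age-standardised score the analysed quantity for bone mineral density, height, weight and growth velocity. Derive such scores for lean mass, body fat and blood pressure where a reference exists. Use the same sex reference at both time points, because switching it between visits would itself create a change.
3. Where no reference exists, use the mixed model already offered instead of a plain paired t-test, with age at visit and Tanner stage at treatment start. Do not adjust for Tanner stage recorded on treatment: treatment alters it, so adjustment would remove part of the change under study. With treated participants only, age and time on treatment advance together within a person, so the age term leans on differences in starting age. The result should therefore still be described as change during therapy.

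Raw-unit changes may be reported alongside.

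The cost is a change of wording and some derived variables; age, sex, height and Tanner stage are already on the extraction list. The drawbacks are dependence on the reference data available and a more modest claim.
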